## Abstract

**Background:**

Older adults with chronic pain, opioid use, and opioid use disorder (OUD) present complex management decisions in primary care. Clinical tools are needed to improve care delivery. This study protocol describes the planned implementation and evaluation of I-COPE (Improving Chicago Older Adult Opioid and Pain Management through Patient-centered Clinical Decision Support and Project ECHO®) to improve care for this population.

**Methods:**

This study uses a pragmatic, expanding cohort stepped-wedge design to assess the outcomes. The study will be implemented in 35 clinical sites across metropolitan Chicago for patients aged ≥ 65 with chronic pain, opioid use, or OUD who receive primary care at one of the clinics. I-COPE includes the integration of patient-reported data on symptoms and preferences, clinical decision support tools, and a shared decision-making tool into routine primary care for more effective management of chronic pain, opioid prescribing, and OUD in older adults. Primary care providers will be trained through web-based videos and an optional Project ECHO® course, entitled “Pain Management and OUD in Older Adults.” The RE-AIM framework will be used to assess the I-COPE implementation. Effectiveness outcomes will include an increased variety of recommended pain treatments, decreased prescriptions of higher-risk pain treatments, and decreased patient pain scores. All outcomes will be evaluated 6 and 12 months after implementation. PCPs participating in Project ECHO® will be evaluated on changes in knowledge, attitudes, and self-efficacy using pre- and post-course surveys.

**Discussion:**

This study will provide evidence about the effectiveness of collecting patient-reported data on symptoms and treatment preferences and providing clinical decision support and shared decision-making tools to improve management for older adults with chronic pain, opioid use, and OUD.

**Trial registration:**

ClinicalTrials.gov NCT04878562.

**Supplementary Information:**

The online version contains supplementary material available at 10.1186/s13063-022-06537-w.

## Administrative information

Sections of this protocol are not numbered with SPIRIT Checklist item numbers, please refer to Additional file 7 for the completed SPIRIT Checklist. Participant timeline is presented in Table 1.

**Table 1 Tab1:** Schedule of enrollment, interventions, and assessments for the I-COPE Project

	Study period								
	Enrollment	Implementation							Close-out
Time point	*March 21*	*September 21*	*November 21*	*January 22*	*March 22*	*July 22*	*September 22*	*November 22*	*November 23*
Enrollment									
Patients			x	x	x	x	x	x	x
Providers	x	x	x	x	x	x			
Interventions									
* Project ECHO Course: I-COPE Step 1*		x	x						
* Project ECHO Course: I-COPE Step 2*				x					
* Project ECHO Course: I-COPE Step 3*				x	x				
* Project ECHO Course: I-COPE Step 4*					x				
* Project ECHO Course: I-COPE Step 5*							x		
* I-COPE Toolkit: implementation step 1*			x	x	x	x	x	x	x
* I-COPE Toolkit: implementation step 2*				x	x	x	x	x	x
* I-COPE Toolkit: implementation step 3*					x	x	x	x	x
* I-COPE Toolkit: implementation step 4*						x	x	x	x
* I-COPE Toolkit: implementation step 5*								x	x
Assessments	x								
* I-COPE toolkit usage*		x	x	x	x	x	x	x	x
* Diversity of provider recommended pain treatments*		x	x	x	x	x	x	x	x
* Prescribed higher-risk pain treatments*		x	x	x	x	x	x	x	x
* Patient-reported pain scores*		x	x	x	x	x	x	x	x
* Provider self-efficacy*		x	x	x	x	x			

The World Health Organization Trial Registration Dataset.

**Table Taba:** 

Data category	Information^32^
Primary registry and trial identifying number	ClinicalTrials.gov NCT04878562
Date of registration in primary registry	7 May 2021
Secondary identifying numbers	IRB20-1580
Source(s) of monetary or material support	Agency for Healthcare Research and Quality
Primary sponsor	Agency for Healthcare Research and Quality
Secondary sponsor(s)	n/a
Contact for public queries	[name], MS [[contact]] University of Chicago
Contact for scientific queries	[name] [[contact]] University of Chicago
Public title	Improving the management of chronic pain, opioid use, and opioid use disorder in older adults (I-COPE): study protocol
Scientific title	Improving the management of chronic pain, opioid use, and opioid use disorder in older adults (I-COPE): study protocol
Countries of recruitment	United States
Health condition(s) or problem(s) studied	Chronic pain, opioid use, opioid use disorder
Intervention(s)	Active comparator: *ICOPE intervention*
	Placebo comparator: n/a
Key inclusion and exclusion criteria	Ages eligible for the study: ≥ 65 years Sexes eligible for the study: both Accepts healthy volunteers: no
	Inclusion criteria: older adult patient (≥ 65 years), diagnosed with chronic pain or conditions associated with chronic pain, high pain Score (> 7) at a previous visit opioid use disorder and/or current opioid use
	Exclusion criteria: none
Study type	Interventional
	Allocation: randomized
	Primary purpose: health services research
	Phase: n/a
Date of first enrolment	June 2021
Target sample size	3040
Recruitment status	Recruiting
Primary outcome(s)	Variety of recommended pain treatments; prescribed higher-risk treatments; patient pain scores
Key secondary outcomes	Reach and adoption of I-COPE tools; safe opioid prescribing measures, primary care providers’ knowledge, attitudes pre- and post- ECHO Chicago course, self-efficacy related to managing older adults with chronic pain, opioid use, and OUD

## Background

Adults aged 65 years or older experience more pain than younger adults, with approximately half of older adults in the USA experiencing chronic pain [1–3]. Chronic pain in older adults can be complex and challenging for primary care providers (PCPs) to manage because older adults are at higher risk for poor outcomes related to multimorbidity and polypharmacy. To manage chronic pain in older adults, opioids may be appropriate. However, caution is needed due to older adults having a higher risk for side effects, greater frequency of opioid-related emergency department visits, and increases in both heroin use and opioid overdose deaths [4, 5].

To facilitate the management of chronic pain in older adults, several key factors need to be incorporated [6, 7]. From the patient standpoint, a thorough understanding of each patient’s goals and preferences, comorbidities, and resources is necessary. Additionally, coordination of care team members and caregivers is important, and usually, combinations of different types of therapies are needed [8]. However, implementation of clinical guidelines in practice can be difficult. Limited visit time, patient and PCP reluctance to change an established routine, and lack of PCP education and training prevent optimal care for chronic pain in older adults [9]. To help improve chronic pain management for older adults, better tools are needed [1, 2, 10, 11]. I-COPE was designed to address these issues through the collection of patient-reported data on symptoms and preferences, and implementation of clinical decision support and shared decision-making tools, with accompanying PCP education.

## Methods

### Intervention study aims

Improving Chicago Older Adult Opioid and Pain Management through PCCDS and Project ECHO® (I-COPE) aims to leverage patient-reported data on symptoms and preferences, clinical decision support tools, and a shared decision-making tool to improve clinical management of chronic pain, opioid prescribing, and OUD in older adults.

### Study design

As part of the development phase of I-COPE, the full workflow and EHR tools are being piloted at two University of Chicago Medicine (UCM) clinics. Pilot phase implementation experiences are being used to improve the I-COPE tools and processes. I-COPE will be implemented in a pragmatic, expanding cohort stepped-wedge trial with a transition period, continuous recruitment, and longitudinal exposure (Fig. 1) [12]. There will be a total of five, 12-week steps with 5 to 9 clinics per step, starting September 2021. All five steps are expected to implement I-COPE by November 2022.

**Fig. 1 Fig1:**
[figure not shown]
I-COPE study design: stepped-wedge study with a transition period

### Study setting and participants

The study will be implemented at 35 clinical sites in the Chicago metropolitan area from Access Community Health Network (ACCESS) or UCM. ACCESS is a federally qualified health center (FQHC) network with 35 clinical sites; all clinical sites that care for older adults (*N* = 32) are participating in this study. UCM is an academic medical center with affiliated community clinics, and 3 out 4 primary care clinics agreed to participate. PCPs include physicians, physician assistants, and advanced practice nurses. Epic® electronic health record (EHR)-based tools for I-COPE were built for both health systems and are available for all PCPs at participating sites. Eligible patients will be identified based on pre-existing EHR data. The inclusion criteria are patients 65 years or older who receive primary care at a study site during the study period and have a pain score ≥ 6 or have diagnoses frequently associated with chronic pain (full ICD-10 list provided in Additional file 1), a current opioid prescription, or have been diagnosed with OUD (full ICD-10 list provided in Additional file 2) (Table 2).

**Table 2 Tab2:** I-COPE study patient inclusion criteria

Criteria^a^	Definition
Age	≥ 65 years
Visit type	Virtual or in-person primary care visits
Chronic pain	• Last visit pain score ≥ 6 in the last 12 months • Diagnosis associated with chronic pain on problem list or past encounter in the last 12 months
Opioid use	Two or more opioid prescriptions in the last 12 months
OUD [2]	OUD diagnosis on problem list, past medical history, or any past encounter

*Abbreviation: OUD*, opioid use disorder

^a^Patients eligible for inclusion must meet age and visit type criteria and at least one of the criteria for chronic pain, opioid use, or OUD definitions

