### Intervention outcomes

The RE-AIM framework will be used to assess the effectiveness of the implementation of I-COPE (Table 3) [24]. Effectiveness outcomes will include an increase in the variety of recommended pain treatments at the clinic and PCP level, decrease in prescribed higher-risk pain treatments (discontinuation or decrease in prescribed daily milligram equivalents of opioids and Beer’s criteria medications), and decreases in patient pain scores (% of patients with high initial pain scores (≥ 6) who experience a 30% reduction in scores) at 6 months (Table 3). Additional outcomes include measures of use (reach and adoption) of I-COPE tools by PCPs and clinics, specific safe opioid prescribing measures, and evaluation of Project ECHO® participants through pre- and post-surveys that include change in PCP knowledge, attitudes, and self-efficacy related to managing older adults with chronic pain, opioid use, and OUD (Table 3). Outcomes will be evaluated again at 12 months to assess sustainability.

**Table 3 Tab3:** RE-AIM framework implementation outcomes used to evaluate the ICOPE program implementation

Framework dimension	Outcome
Reach	• # and % of eligible patients who complete the pre-visit questionnaire • # and % of eligible PCPs who use the I-COPE order set • # and % of PCPs participating in ECHO-Chicago
Effectiveness	• Change in a variety of recommended pain treatments • Change in prescribing of higher-risk pain treatments (opioids and Beer’s criteria medications) • Change in pain scores o % with chronic pain diagnoses and high initial pain scores (≥ 6) who experience a 30% reduction in scores in 6 months • Change in safe opioid prescribing practices o Annual drug screens in a patient with chronic opioid use o Naloxone prescribing in patients with > 50 MME equivalents of opioids or OUD o Co-prescribing of opioids and benzodiazepines • Change in self-efficacy and practice behaviors for ECHO-Chicago participants
Adoption	• # and % of clinics who use the I-COPE Program
Implementation	• # and % of eligible patients who received all I-COPE tools (pre-visit questionnaire and order set use) • # and % of PCPs who participated in ECHO-Chicago and attended all eight sessions
Maintenance	• Outcomes listed above at 12 months

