### Sample size

We calculated the sample size for the effectiveness outcome that had pre-intervention data, change in patient pain scores (% of patients with high initial pain scores (≥ 6) who experience a 30% reduction in scores) at 6 months, using the sample size calculation method for closed cohort (a special case of expanding cohort) by Hooper et al. [25] and Hooper and Bourke [26]. We estimated that there were an average of 26 PCPs and about 600 patients per step. We expect that at least 68% of older adults with pain scores ≥ 6 experiencing ≥ 30% pain score reduction due to the intervention. The total sample of 3040 eligible patients within 5 steps is needed to ensure at least 80% power to detect the difference of 10% at a one-sided significance level of 5%. Given a total of > 3400 patients with baseline pain score ≥ 6 in the 35 sites, the power becomes much larger. More detailed information is available in the Additional file 6.

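### Patients can first qualify after their unit's launch on rolling records made in an exposed clinic, so the intervention may alter who is in the intervention-period cohort

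*Protocol article*

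**What the plan says.** The Study design section describes a "pragmatic, expanding cohort stepped-wedge trial with a transition period, continuous recruitment, and longitudinal exposure". Under Study setting and participants, "Eligible patients will be identified based on pre-existing EHR data".

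Table 2 requires age and visit type plus any one of the clinical criteria. The time limits are:

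- Pain score: "Last visit pain score ≥ 6 in the last 12 months".
- Pain diagnosis: "Diagnosis associated with chronic pain on problem list or past encounter in the last 12 months".
- For prescribing, the route into the cohort is "Two or more opioid prescriptions in the last 12 months".
- Opioid use disorder (OUD): "OUD diagnosis on problem list, past medical history, or any past encounter", with no look-back limit.

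None of these is anchored to a launch date. Under Data collection, data are taken on all eligible patients seen from 6 months before the step 1 launch to 12 months after the step 5 launch.

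Under Intervention outcomes, effectiveness includes a "decrease in prescribed higher-risk pain treatments", which covers stopping or lowering opioids. It also includes the share of patients with an initial pain score of at least 6 whose score falls by 30%. No date is given for that initial score.

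The sample size was found "using the sample size calculation method for closed cohort (a special case of expanding cohort").

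**The concern.** In a stepped wedge with continuous entry, randomising units balances the units. It does not balance patients who become eligible later on records made after launch. If the intervention changes those records, it can change who enters, and the two conditions then compare different kinds of patient. Intention-to-treat does not repair this, because it governs how patients are analysed once they are in the cohort.

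The opioid criterion is the clearest case. A clinic that succeeds in reducing opioid prescribing may have fewer patients reaching two prescriptions. Those who still reach two may be the ones whose prescribing is hardest to change. That could hide a real effect on the opioid outcome.

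For pain, the response is conditioned on a score that is also an entry variable. A shift in which scores bring patients in after launch could move the response rate in either direction.

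**Working it through.** **1. How much of the look-back lies after launch.** Table 1 shows toolkit implementation starting in November 2021, January 2022, March 2022, July 2022 and November 2022, with close-out in November 2023. The five steps therefore have T = 24, 22, 20, 16 and 12 exposed months. For a patient qualifying m months after launch, the share of the 12-month window lying after launch is min(m/12, 1). Summed over exposed time, this gives 6 + (T − 12) month-equivalents:

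| Step | T | 6 + (T − 12) | Average share after launch | Months with window wholly after launch (T − 12) |
|---|---|---|---|---|
| 1 | 24 | 18 | 75% | 12 |
| 2 | 22 | 16 | 73% | 10 |
| 3 | 20 | 14 | 70% | 8 |
| 4 | 16 | 10 | 63% | 4 |
| 5 | 12 | 6 | 50% | 0 |
| All | 94 | 64 | 64/94 = 68% | 34 (34/94 = 36%) |

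This weights all exposed months equally. It describes calendar time and does not measure differential entry.

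**2. The plan's own sample-size figure.** The article gives 3040 patients for at least 80% power, a 10-point difference and one-sided 5%. Taking 58% against 68% (the 58% is inferred as 68 − 10), an individually randomised comparison needs 288 per arm, 576 in total. The ratio 3040/576 is 5.28. The correlations behind that ratio are not in the article, which refers to Additional file 6, so 3040 can be neither confirmed nor refuted here. The point does not depend on it.

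**3. Standard error implied by the stated power.** SE = 10 / (1.645 + 0.842) = 4.02 points. If true power exceeds 80%, the SE is smaller and a given bias weighs more.

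**4. What a bias of b points would do to the pain outcome.** Type I error = 1 − Φ(1.645 − b/SE). Power, if the bias works against the intervention, = Φ((10 − b)/SE − 1.645).

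| b (points) | Type I error | Power if bias is in the opposite direction |
|---|---|---|
| 0 | 5% | 80% |
| 1 | 8.1% | 72.3% |
| 2 | 12.6% | 63.5% |
| 3 | 18.4% | 53.8% |

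**5. What b might be.** To first order, b = f × d. Here f is the share of exposed patients who are post-launch entrants, and d is the non-causal difference in their response rate. The documents give neither. Over an assumed range of f = 10% to 50% and d = 3 to 15 points, b runs from 0.10 × 3 = 0.3 to 0.50 × 15 = 7.5 points. A 2-point bias corresponds, for example, to f = 20% and d = 10.

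**6. Is a pre-launch cohort feasible?** For pain, the article counts more than 3400 patients with a baseline score of at least 6, which is at least 360 above 3040. For the other outcomes it gives no such count.

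**The case against.** The strongest reply is that the route into the cohort is narrow. The pre-visit questionnaire is assigned only to patients who are already eligible, and only its completion triggers the alert. A reader might infer that screening brings in milder or newly coded patients. The documents do not support that: a screened patient is already in, and nothing says that the tools prompt diagnoses. What remains is indirect. The tools are open to all providers at a site, and training covers general principles of pain management, so care can change before a patient qualifies.

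The criteria are also alternatives. Lower prescribing keeps a patient out only if that patient has no qualifying pain score, pain diagnosis or OUD diagnosis. Diagnoses carried on the problem list are less open to change. Patients who entered before launch contribute to both conditions. All of this stands and limits the effect.

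The 10-point benchmark belongs to pain alone. Patients who enter on opioids, diagnosis or OUD without an initial score of at least 6 are not in that denominator. This stands too: step 4 of the working sizes the pain outcome, while the mechanism is strongest for the opioid outcome, where the article gives no target to compare with.

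Finally, an expanding cohort is a declared design, and rules for later entrants commonly sit in the analysis plan. The absence of such a rule from the article is therefore not the finding. The finding is that the eligibility rule, as stated, lets records made after launch decide entry on variables that are also outcomes.

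**Conclusion.** The point holds as a risk. Entry continues after launch, three criteria use a rolling look-back that lies mostly after launch in exposed months, and two entry variables are also outcomes. Neither randomising units nor intention-to-treat removes selection of this kind.

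A reader might go further and conclude that the cohorts do differ. The documents do not show that. They give neither the share of post-launch entrants nor the size or direction of any shift, and every figure for f and d above is assumed. The firmer statement is about sensitivity: with an SE near 4 points, a bias of 2 points is enough to move the one-sided type I error from 5% to about 12.6%.

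A reader might also infer from the closed-cohort calculation that a pre-launch cohort is what was powered throughout. That does not follow. The article treats the closed cohort as a special case for calculation, and the count above 3400 applies to the pain outcome only.

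**What to change.** Keep the expanding-cohort analysis as the main one, and pre-specify the following beside it:

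1. A supporting analysis of each effectiveness outcome, limited to patients who met Table 2 on data recorded before their own unit's launch. Use the cohort identified before the step 1 launch as a stricter check.
2. For the 6-month pain response, a dated initial score. For exposed windows, take the last score before that unit's own launch. For control windows, take the last score before a window that ends before launch.
3. A table of new entrants per unit and period by entry criterion, to show any shift at launch.
4. A statement that the conclusion will be qualified if the two analyses disagree.

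The initial score should not be frozen at the step 1 launch for every unit. Six months from November 2021 ends around May 2022, before steps 4 (July 2022) and 5 (November 2022) launch, so those steps would have no exposed 6-month outcome. Item 2 lets all five steps contribute one.

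The cost is small. The work is added analyses and a table, on EHR data already planned for extraction. Scores that precede the earliest step 1 control window may lie before the 6-month pre-launch data period, so the extraction should reach back far enough to supply them. Post-launch entrants do not contribute to the supporting analysis, so it is less precise than the main one. For outcomes other than pain, its size cannot be judged from the article.

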### Intervention

#### Development of I-COPE

I-COPE was developed using an iterative design approach over a 9-month period. The design of I-COPE was led by a multidisciplinary team of investigators with input from a stakeholder advisory panel. The I-COPE team includes experts in geriatrics, palliative medicine, primary care, clinical informatics, shared decision-making, medical education, addiction medicine, behavioral medicine, implementation science, and clinical research. The stakeholder advisory panel included additional content experts, as well as three older adult patients. In addition, specialists in the Epic® EHR system were involved.

#### I-COPE tools

I-COPE includes a pre-visit patient questionnaire that PCPs can review to enable shared decision making, alongside clinical decision support, to create a comprehensive pain, opioid, and opioid use disorder management plan.

##### Patient-reported data on symptoms and preferences (pre-visit questionnaire)

*Questionnaire contents.* Eligible patients receive a pre-visit questionnaire that asks about pain symptoms, goals for pain management, pain treatment preferences, depression symptoms, and opioid and illicit drug use (Additional file 3). The questionnaire uses validated screeners to ask about current levels of pain (Pain, Enjoyment of Life, General Activity (PEG) scale), depression (PHQ-2), and drug use (drug abuse screening test (DAST-2) (ACCESS) or single-question drug use screener (UCM)) [13–15]. The I-COPE questionnaire also asks patients to identify functional goals that might be achieved through better pain management, and treatment preferences ranging from self-management to surgical intervention.

*Questionnaire administration.* The pre-visit questionnaire will be automatically assigned to eligible patients when they schedule a clinic appointment. Three days before their clinic appointment, eligible patients who have an active patient portal account will be invited to complete the pre-visit questionnaire. If patients do not complete the questionnaire before their appointment or they do not have an active patient portal account, they will be asked to complete the questionnaire at check-in either on paper or using electronic tablets, depending on the workflow in that clinic. Medical assistants will enter paper responses into the Epic® EHR. A caregiver may help the patient complete the questionnaire if necessary.

